### Recruitment, consent and screening

Participants will be recruited through different approaches: (1) Participants will be approached and recruited through the support of community organisations in Manchester. (2) Participants who have already taken part in the first stage of this project through interviews and have given explicit consent to be contacted for future studies will be contacted to inform them about the intervention study. (3) Recruitment advertisements will be posted in Chinese community centres and Chinese-speaking churches. (4) Advertising will also take place through study-specific social media accounts and platforms such as the Chinese social media app WeChat. Participants will also be recruited through word-of-mouth approaches.

Any interested participants can contact the researcher directly and will be provided a copy of the participant information sheet (PIS). Potential participants will be given at least 24 h to decide whether or not to take part. Potential participants who are interested in the study will be asked to provide written consent (Appendix 1). After signing the consent form, participants will be asked to answer a series of screening questions to determine their eligibility. Once eligibility is confirmed and interest is reaffirmed, baseline data will be collected. A gift voucher will be provided to participants who complete the assessment, which aims to improve recruitment rates and reduce dropout rates. A convenience sampling approach will be utilised. We will strive to recruit participants from a broad spectrum of demographics, including gender, age, PA level, and language backgrounds, encompassing speakers of Mandarin and Cantonese.

### Sample size

The determination of the sample size is driven by practical considerations and the need to obtain meaningful insights into the feasibility aspects of the larger trial, which is different from estimating effects or hypothesis testing in an RCT that requires robust sample calculation. There is limited guidance on determining the sample size for feasibility trials. A recent review shows that the median target sample size of pilot and feasibility studies was 30 (with an interquartile range of 20–50) per arm [12]. Julious (2005) proposed a rule of thumb of 12 participants per group [13].

Considering the timeline of the project, it is essential to balance sample size requirements with time constraints.

We aim to include at least 12 participants per study arm, totalling 24 participants. To account for an anticipated 20% dropout rate, we will recruit at least 30 participants. Assuming a retention rate of 80% with a sample size of 30, the 95% confidence interval for the number of retained participants is approximately 19 to 27.

This study targets older Chinese adults in the UK with insufficient PA. Chinese as an ethnic minority group in the UK is often considered a hard-to-reach group for research. Based on insights from the PCIE presentations, recruiting physically inactive Chinese adults presents even greater challenges, as those who are used to sedentary lifestyles are reluctant to participate in any activities, including research.

**Fig. 1 Fig1:**
[figure not shown]
Flow of participants through the study

### Blinding

Blinding refers to the process of concealing the allocation of participants to different study arms from the participants and/or the researchers involved in the study to ensure the validity of the study results [17]. However, considering the PA promotion strategies are “active” interventions, which will be delivered by the leader researcher, therefore, it is not possible to blind either the participants or the researcher.

The baseline assessment will be conducted before randomisation, ensuring the data collection occurs before any interventions are introduced. Subsequently, outcome assessments will be conducted by the lead researcher, with support from a research assistant who is unaware of the randomised group assignments. This approach is intended to minimise bias in the outcome assessment process and enhance the validity of the study’s findings. The lead researcher will carry out the data analysis. Although the “blinding” strategies cannot be employed in the trial due to the nature of the PA promotion intervention, we will strive to minimise biases through clear instructions, standardised procedures, and transparent reporting of blinding procedures to enhance the validity and reliability of the study findings.

### Intervention group

Participants randomised into the intervention group will receive the culturally appropriate PA promotion package. The strategies in the package were developed based on 27 BCTs and will be delivered through three parts: a series of booklets, three workshops, and a virtual social media support group. The intervention content is presented in Table 2.

**Table 2 Tab2:** The intervention content table

Component	COM-B	Intervention functions	Behaviour change techniques	Intervention description	Evidence from the qualitative interview with the target population
**Booklet**					
**Booklet- page 1**	**Capability**	Education Persuasion	5.1. Information about health consequences 5.3. Information about social and environmental consequences 5.6. Information about emotional consequences	A page introduces the health, social, and emotional benefits of PA and encourages participants to identify the benefits most relevant to their personal needs	“*I wonder if physical activity is really that important. The older lady who lives next door is 94 years old, she never exercises but is very healthy. So, is PA really that important?”*
	**Motivation**				
** Booklet-page 2**	**Capability **	Education	9.1. Credible source	A page provides information about the WHO PA recommendations for older adults	*“I don’t know how much PA I should do; I believe older adults should only walk slowly….”* *I think most older adults pay little attention to the guidelines…*
	**Motivation**				
** Booklet-page 3**	**Motivation **	Education Modelling	1.1. Goal setting (behaviour) 1.2. Problem-solving	A page to help participants identify the gap between their current PA level and the recommended PA guidelines A page guides participants in identifying the barriers they face in attending PA	*“I can check how many steps I’ve taken on my phone, so I set a target, like 10,000 steps each day. Then I walk with the purpose of achieving my target. I think this motivates me”* *Chinese seniors in the UK are a diverse group and face various barriers when attending PA*
	**COM-B problems identified**				
** Booklet-page 4**	**Opportunity**	Education Enablement	1.2. Problem-solving 8.3. Habit formation	A page offers tips on how to integrate PA into daily life	“*Physical activity is not really part of my routine. I have to take care of my grandchildren, so how can I find time to exercise?”*
	**Capability**				
** Booklet-page 5**	**Capability**	Education	4.1. Instruction on how to perform the behaviour	A page introduces safety tips for older adults participating in PA	*“PA may be dangerous for our older adults. Many older adults, like me have high blood pressure, and it’s dangerous when my heartbeat increases”* “*Falling is my biggest concern* *My husband passed away two weeks in the hospital after he fell in the garden. I believe safety is the most important thing.”*
	**Motivation**				
** Booklet—page 6**	**Motivation**	Education Modelling	5.1. Information about health consequences 5.3. Information about social and environmental consequences 6.2. Social comparison 16.3 Vicarious consequences	A page provides examples/stories of how PA has benefited other Chinese seniors in the UK in terms of health, social connections, and emotional well-being	“*What’s the point? I used to be very active, but my husband died two years ago. I just don’t have interest in anything, including physical activity*” *“I’ve worked very hard my whole life, and now I’ve just become a bit lazy, you know? I just want to take it easy, like watching TV or playing mahjong with my friends.”*
** Booklet—page 7**	**Opportunity**	Enablement	3.1. Social support (unspecified)	A page offers guidance on how to find additional support, such as from family members, peer support and the health care system	“*I’m not really sure what type of exercise suits me, and the GP usually doesn’t discuss exercise with me. You know, the appointment time is very limited*.” *“I live by myself, and my grandson calls me to remind me to exercise every morning… so I just walk around inside my house.”*
** Booklet—page 8**	**Opportunity**	Enablement	3.1. Social support (unspecified) 7.1. Prompts/cues	A page provides information about existing local Chinese PA programmes	“*I just moved to the UK. I enjoyed exercising when I was in Hong Kong, but I don’t know about the exercise programs here. If I knew, I would love to join*.”
** Additional booklet-** Otago Exercise Booklet	**Capability**	Training	4.1. Instruction on how to perform the behaviour 9.1 Credible source	The Chinese version of Otago Home Strength and Balance Booklet	“*I only walk, and I walk at least half an hour a day. I don’t know how to do strength and balance exercises.”* *“Sometimes, I follow exercise videos on my phone, although I’m not sure if I’m doing them correctly*.”
** Additional booklet –** PA Logbook	**Motivation**	Enablement	1.1. Goal setting (behaviour) 1.4. Action planning 1.5 Review behaviour goal(s) 1.6 Discrepancy between current behaviour and goal 2.3. Self-monitoring of behaviour 2.5. Self-monitoring of outcome(s) of behaviour 5.4. Monitoring of emotional consequences	Provide a PA logbook for setting targets, monitoring PA behaviour, and tracking achievement, such as improvements in balance, strength, and emotional well-being	“*I was very busy and worked hard when I was young, and now that I’m retired, I prefer quiet activities, like watching TV. I enjoy my life, but physical activity has never been a part of it*.”
	**Capability**				
**Workshop**					
** Presentation**	**Capability**	Education Persuasion	1.2. Problem-solving 5.1. Information about health consequences 5.3. Information about social and environmental consequences 15.1. Verbal persuasion about capability	The researcher will give a short presentation during each workshop to introduce the information in the booklet, helping participants better understand the content	“*You know, some older adults may not enjoy reading, and some of us have poor eyesight or low literacy level. So they may not be able to read…”* *“I think gathering people together for a lecture would be more effective, and it would also provide an opportunity for people to meet each other.”*
	**Motivation**				
** Group discussion**	**Motivation**	Persuasion Modelling	3.1. Social support (unspecified) 6.2. Social comparison 12.2 Restructuring the social environment	Participants will be able to discuss their physical activity during each workshop and share their PA experiences	“*I think gathering together like today to talk about PA is very interesting. When I hear about others doing so much exercise, I feel like I also need to exercise. You know, I want to be healthy too”*
** Exercise demonstration**	**Capability**	Training	2.2. Feedback on behaviour 4.1. Instruction on how to perform the behaviour 6.1. Demonstration of the behaviour 8.1. Behavioural practice and rehearsal 9.1 Credible source	A Chinese-speaking physiotherapist will be invited to demonstrate how to perform the Otago strength and balance exercises	“*You know, if you can invite a professional to show us how to exercise, we would be more likely to believe it. The most important thing is to design something that is really reliable, so we can trust it. Otherwise, people may not listen to you*”
**Social media support group**					
** Encourage/remind message from the researcher**	**Motivation**	Persuasion Incentivisation	3.1. Social support (unspecified) 3.2. Social support (practical) 3.3. Social support (emotional) 7.1 Prompts/cues 10.4. Social reward	The researcher will send messages to encourage participants to set targets, offer verbal rewards for completing their PA targets, and reminders of the coming PA programmes	“*Sometimes, I just forget to exercise* *I just don’t like to exercise, my grandson always calls me to encourage me to do some exercise, so I will walk around in the room.”*
	**Opportunity**				
** Group discussion**	**Motivation**	Environment restructuring modelling	3.1. Social support (unspecified) 6.2. Social comparison 12.2 Restructuring the social environment	Participants are encouraged to discuss their PA targets and behaviours within the group to seek peer support	*“You know, where I live, there’s no one else who speaks Chinese at my age. I really hope to find an exercise buddy so we can encourage each other. I think WeChat friends can be an alternative approach*”
	**Opportunity**				
**Other strategies**					
** Strength band**	**Opportunity**	Enablement	12.5. Adding objects to the environment	Participants will be offered a strength band to enable them to do strength and balance exercises at home	“*For them who cannot leave home to do exercise, you can teach them how to do exercise at home, for example, provide the strength band like this, it is very useful*.”
** Pedometer**	**Opportunity**	Enablement	2.3. Self-monitoring of behaviour 12.5. Adding objects to the environment	Participants will be offered a pedometer to enable them to self-monitor their PA behaviour	“*My smartphone can help me monitor how many steps I walk, and I check it often. I think it’s a good tool*.” “*Many of us received fitness trackers, but we don’t like using them. The screen is too small to read, and you have to charge it all the time.*”
	**Motivation**				
** Language support**	**Opportunity**	Enablement	3.2. Social support (practical) 12.2. Restructuring the social environment	All the information will be provided in accessible languages, including Traditional and Simplified Chinese	“*There is information available in English, but I cannot read it. There are local PA programs, but I’m not interested.”*
	**Capability**				

#### The booklet

The detailed content of the booklet is presented in Table 2. The developed booklet will include three parts: a culturally appropriate core booklet, the Chinese version of the Otago home exercise booklet, and a PA logbook. The information in the booklets was from reliable resources, including the UK Chief Medical Officers’ PA Guidelines [18], and the WHO PA guidelines [19]. The booklet also incorporates Chinese cultural factors. For example, it explains the importance of PA from the perspective of traditional Chinese medicine and philosophy and provides resources for traditional Chinese exercise programmes. A Chinese version exercise instruction booklet was translated based on the Otago home exercise booklet produced by Later Life Training [20]. Participants are also provided with a logbook to plan their PA, record daily PA, and track their achievements. All booklets are available in user-preferred languages, including Traditional and Simplified Chinese.

#### Workshop

Participants will be invited to attend three workshops during a 12-week period, scheduled every 4 weeks. Workshops will be designed to directly deliver the knowledge and information provided in the booklet. The workshop will include presentations, group exercises, and group discussions. When designing the content of the three workshops, we also considered the Transtheoretical Model (Stages of Change) [21]. This model has been used to design a walking group for older Chinese immigrants in the USA [22]. The workshops will progress from building awareness and capability (workshop 1), to planning and overcoming barriers (workshop 2), and maintaining PA and preventing relapse (workshop 3). A Chinese-speaking physiotherapist will be invited to demonstrate strength and balance exercises from the Otago home exercise programme [20, 23]. The workshop also serves as an avenue for older Chinese adults to connect, find exercise partners, and cultivate peer support before they are invited to the social media group. Each workshop will last about 90 min.

#### Social media group

Participants will be invited to join a study special WeChat group (WeChat is a popular social media platform among the Chinese population) or WhatsApp group as an online peer support platform for participants to share their PA targets and progress and encourage each other, and also receive motivational messages and reminders about upcoming PA programmes from the researcher. Participants can choose to use the social media platform they are familiar with, either WeChat or WhatsApp.

In addition, participants will receive a resistance band to complete the strength exercises from the Otago programme, and a pedometer, which serves as both an intervention component by supporting behaviour monitoring and goal setting, and a tool for data collection.

### Control group (WHO leaflet group)

In the control group, participants will receive the printed leaflet of recommendations from the WHO on PA for older adults [19]. Participants will be encouraged to follow these guidelines, 150–300 min of moderate or 75–150 min of vigorous aerobic activity per week, along with balance and strength exercises twice weekly, at a time and place convenient to them. No additional support will be provided. Participants in the control group will also be provided with pedometers to collect their steps at the three time points.

The study will span 18 weeks, comprising a 12-week intervention phase and a 6-week follow-up phase. During the intervention phase, participants in the intervention group will attend workshops and receive motivational and reminder messages via a social media group. In the follow-up phase, they will be encouraged to continue their PA behaviour independently without further workshops or messages. Participants in the control group will be encouraged to follow the WHO PA guidelines during the 18-week study period and, after the study concludes, will receive the culturally appropriate PA booklet and be invited to attend one workshop.

### Data collection

Baseline screening and measurements will be conducted for all eligible participants before randomisation (T1). Subsequently, measurements will be taken at two additional time points: post-intervention (T2, 12 weeks after randomisation) and after the follow-up period (T3, 18 weeks after randomisation). A summary of the schedule of enrolment, interventions, and assessments is presented in Table 3.

**Table 3 Tab3:**
[figure not shown]
Schedule of enrolment, interventions and assessments

*Abbreviation:*
*PA* physical activity, *COM-B* Capability, Opportunity, Motivation, and Behaviour, *SPPB* Short Physical Performance Battery test, *CASP-12* Control, Autonomy, Self-realisation, and Pleasure-12 *Participants’ physical activity was monitored for 7 consecutive days from this point

#### Sociodemographic

Sociodemographic information will be collected at baseline. The data collection table will be constructed based on the suggestions of PROGRESS plus [24] and information about participants’ migrant status and language proficiency. The following information will be collected, including, for example, age, gender, employment status, years of education, language spoken at home, fluency in English, years of residence in the UK, medical history and fall history within the past 6 months, and current PA level. We will also collect information on participants’ general practice (GP) details so that in the event of any adverse effects, we can report these to their GP promptly when necessary.

#### Primary outcomes

##### Feasibility outcomes

Recruitment rate, compliance rate, adherence, and follow-up rates will be monitored throughout the entire study, including the recruitment, screening, intervention, and follow-up periods.

##### Recruitment rate

We aim to recruit at least 30 participants within 8 weeks. Detailed records will be kept of the total number of potential participants approached by the researcher, the number of participants who attend the screening, and the number of participants who are ultimately included in the study.

##### Retention rate

Randomised participants may exit the trial for various reasons. A research journal and case report form will be created to record the number of participants who (1) complete all the follow-up data collection; (2) fully withdraw, where participants refuse to engage in any future activities (including intervention and assessment); (3) loss to follow-up, which should only be considered after the 12-week and/or 18-week visits are due and all contact attempts have been exhausted, but still cannot complete the data collection; and (4) death or other serious adverse events. It is recommended not to automatically treat all withdrawals as a complete exit from the trial [25]. Participants should not be fully withdrawn for discontinuing or noncompliance with the intervention. For example, participants may choose to withdraw from attending the workshop or participating in the social media group, but may still be willing to engage in data collection activities. Alternatively, their participation may need to be discontinued based on clinical judgement. We will make every effort to collect as much data as possible to maintain the integrity of the study. The reasons for participants’ exit from the trial will be carefully recorded separately.

##### Adherence

Adherence to the PA protocol will be determined based on the type of intervention [26]. In this study, adherence will be mainly assessed by the number of workshops attended by the participants.

##### Qualitative interviews

At the end of the study, about 50% of participants (including those who withdraw from the trial) will be invited for follow-up interviews. The majority of participants will be from the intervention group. We aim to recruit participants with different adherence levels to gain a comprehensive understanding of their experiences. We will also invite a small number of participants from the control group to understand their experience of being randomised to the control group and how the WHO PA booklet influences their PA levels.

The interview aims to explore older Chinese adults’ experiences of participating in the trial, their overall perceptions of the PA promotion strategy package, and the potential impact the intervention may have had on their PA behaviour. The interview topics will be developed based on the guidance suggested by O’Cathain et al. in 2015. The following topics will be discussed: (1) the recruitment and randomisation process; (2) the PA promotion intervention and ideas for improvement of the intervention; (3) the outcomes and measurements [27].

##### PA behaviour outcomes (T1, T2, and T3)

PA level will be measured three times, at the baseline, after the intervention and after the follow-up. PA, being a multi-dimensional construct, presents challenges when attempting to measure all its facets using a single method. As recommended by Sylvia et al. in 2014, this study will employ a combination of objective and subjective methods to assess participants’ PA levels before and after the intervention [28]. Considering the potential discrepancies, we will prioritise the objective pedometer scores. However, qualitative interviews will be conducted to explore and explain the underlying causes of discrepancies.

##### Subjective measures of PA

Subjective measurement will be conducted using the Chinese version of the Physical Activity Scale for the Elderly (PASE). PASE is a brief and easily scored survey designed specifically to assess the PA of persons aged 65 years and older [29].

Numerous self-reported PA questionnaires have been documented in the literature. A recent systematic review published in 2020 analysed the measurement properties of 40 self-administered questionnaires that assess PA in older adults. This review suggested that PASE demonstrated sufficient reliability and validity, making it a suitable choice to assess total PA in this study [30]. In addition, it is worth noting that a Chinese version of the PASE questionnaire was published in 2012 [31]. This further strengthens the appropriateness of using the PASE questionnaire as a measurement tool for assessing PA in this study.

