**Methods/design:**

This is a two-arm pragmatic feasibility RCT. Community-dwelling individuals who self-identify as Chinese, reside in the UK, are aged 60 years and older, and do not meet the World Health Organization (WHO) PA recommendations (i.e. < 150 min moderate PA or balance/strength exercise < 2 times per week) will be recruited. Participants will be randomised to receive either the culturally appropriate PA promotion strategy package or the WHO PA recommendation leaflet. Outcome data will be collected at baseline, 12 weeks, and 18 weeks post-randomisation. Primary outcomes will include feasibility measures (e.g. recruitment, compliance, adherence, and follow-up rates), intervention acceptability (qualitative interviews), and both subjective PA levels (PA Scale for the Elderly) and objective PA levels (Realalt 3DTriSport 3D Pedometer). Secondary outcomes will include the Brief COM-B (Capability, Opportunity, Motivation—Behaviour) questionnaire, physical function assessments (Short Physical Performance Battery, SPPB), and quality of life (Control, Autonomy, Self-realisation, and Pleasure-12,CASP-12). The feasibility of the study will be evaluated based on the pre-specified progression criteria.

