#### Eligibility criteria for participants

We will recruit participants who meet the following inclusion criteria:Adults aged 60 years or above;Self-identified as Chinese ethnicity;Speaking either Cantonese, Mandarin, and/or English;Able to read and write Chinese or English;No time requirement for their stay in the UK, but they should have settled in the UK as residents and not as tourists.Self-report not meeting the PA guidelines for older adults (engaging in less than 150 min of moderate-level PA each week and performing balance, strength, and flexibility exercises less than twice a week);Self-report being able to walk around at home independently;Can provide informed consent.

We however will exclude:Those who self-report that they already meet the PA guidelines (engaging in more than 150 min of moderate-level PA each week and performing balance, strength, and flexibility exercises more than twice a week), as this study focuses on older Chinese adults with insufficient PA.Those who plan to be away from Manchester for more than 2 months during the intervention period.Participants with diseases where exercise is contraindicated will be excluded to ensure the safety of the participants (see Table 1). A self-reported approach will be used to identify these conditions, including cognitive impairment, as it is considered more acceptable by PCIE participants than formal assessments such as the MMSE (Mini-Mental State Examination), which were viewed as burdensome. To mitigate potential bias, the research team will monitor participants throughout the study. Participants who show signs of impairment after giving consent, such as difficulty completing data collection or following instructions, will be excluded.

**Table 1 Tab1:** List of conditions contraindicating exercise participation

Participants who self-report any of the following diseases will be excluded:
o Uncontrolled pain;
o Uncontrolled angina;
o Major heart surgery in the last 6 months
o Resting SBP > 180 mmHg or resting DBP > 100 mmHg
o Tachycardia > 100 bpm
o Acute systemic illness (cancer, pneumonia)
o Visual or vestibular disturbances
o Significant drop in BP during exercise
o Unstable or acute heart failure
o Unable to maintain seated upright posture due to neurological deficits
o Recent injurious fall without a medical examination
o Serious impaired cognition (to the extent of being unable to follow simple movement instructions)

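### English-only readers are eligible, but the subjective primary activity measure is fixed to the Chinese version of PASE

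*Protocol article*

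**What the plan says.** Under Eligibility criteria for participants, the protocol article sets two language criteria: "Speaking either Cantonese, Mandarin, and/or English" and "Able to read and write Chinese or English". Someone who speaks and reads only English meets both.

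The abstract lists, among the primary outcomes, "both subjective PA levels (PA Scale for the Elderly) and objective PA levels (Realalt 3DTriSport 3D Pedometer"). Under Subjective measures of PA, one language version is named for everyone: "Subjective measurement will be conducted using the Chinese version of the Physical Activity Scale for the Elderly (PASE").

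Four other places bear on the point:

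- Sociodemographic: the baseline data include "language spoken at home, fluency in English, years of residence in the UK", but no rule links these to the questionnaire version.
- Subjective measures of PA: the choice of PASE is supported by a review that "analysed the measurement properties of 40 self-administered questionnaires that assess PA in older adults". How PASE will be administered in this trial is not stated.
- Blinding: "outcome assessments will be conducted by the lead researcher, with support from a research assistant". The assistant is described as unaware of allocation.
- PA behaviour outcomes: "Considering the potential discrepancies, we will prioritise the objective pedometer scores".

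**The concern.** The eligibility rule and the instrument rule do not fit together. Followed to the letter, the plan can enrol someone and then hand that person a primary-outcome questionnaire in a language they cannot read. The form might then be left incomplete, or be rendered informally into English. An informal rendering is no longer the instrument that the article names and justifies.

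This matters more in a feasibility trial than the small numbers suggest. One of the research questions in the Introduction is whether the outcome measures are appropriate and acceptable for this population. If some PASE forms are incomplete because of a language mismatch, the trial may blame the questionnaire for a problem that lies in the choice of version. The full-scale trial could then inherit the mismatch.

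**Working it through.** The plan gives no figure on this point to reproduce. The main check compares the text; the arithmetic only bounds the size.

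**1. The passages side by side.** Eligibility treats Chinese and English as alternatives, for speech and for literacy. The outcome section names Chinese only. Elsewhere, language choice is offered for the booklets (The booklet) and in the language-support row of Table 2, and both are intervention materials. No section names an English PASE. The Introduction describes a population that includes people who came to the UK young and aged there, and eligibility sets no minimum or maximum stay. English-only readers are therefore possible, though not shown to be present.

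**2. How many might be affected.** The article gives no share, so assume a share *s* and independent recruitment of 30 people (Sample size). The expected number is 30*s*, and the chance of at least one is 1 − (1 − *s*)^30.

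| Assumed *s* | Expected number | Chance of at least one |
|---|---|---|
| 1% | 0.3 | 26% |
| 5% | 1.5 | 79% |
| 10% | 3.0 | 96% |
| 20% | 6.0 | >99% |

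**3. Effect on PASE itself.** If *m* of 30 leave PASE blank at all three visits, its completeness before any dropout is at most (30 − *m*)/30: 96.7% for *m* = 1, 90.0% for *m* = 3, 86.7% for *m* = 4 and 80.0% for *m* = 6. Each person costs 1/30 = 3.3 points.

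**4. Effect on the progression criterion.** Table 4 sets the Go level at 90% of the data, not of each instrument. Five measures are taken at each visit: PASE, pedometer, Brief COM-B, SPPB and CASP-12. Assuming equal weights, the loss in overall completeness is (*m*/30)/5.

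- *m* = 1: 0.7 points, leaving 99.3%.
- *m* = 4: 2.7 points, leaving 97.3%.
- *m* = 6: 4.0 points, leaving 96.0%.
- *m* = 15: 10.0 points, leaving 90.0%, still Go.
- *m* = 16: 10.7 points, leaving 89.3%, Amend.

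Equal weighting is not critical. If PASE carries weight *w*, the loss is *w* × *m*/30. For four blank forms to cost more than 10 points, *w* would have to exceed 0.10 × 30/4 = 0.75, that is, three quarters of all data collected. Four blank forms would matter only if other losses had already brought completeness to between 90% and 92.7%.

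**The case against.** The strongest reply is that the problem may never arise. Recruitment runs through Chinese community organisations, Chinese-speaking churches, WeChat and earlier interviewees, and the section on recruitment singles out Mandarin and Cantonese speakers. People who migrated young have not necessarily lost Chinese literacy. The pedometer takes priority over PASE, no between-group comparison is planned, and the extent of missing data and the reasons for it will be reported. A journal article also condenses a fuller protocol. All of this limits the consequences. It does not remove the conflict, because the article is not silent on the version: it states one, and that version does not serve everyone its own criteria admit.

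Three stronger readings are tempting and are not supported.

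- *That four or more English-only readers would put the trial below the Go level for data completeness.* This applies the 90% level to PASE alone, whereas Table 4 applies it to the data as a whole.
- *That the unblinded lead researcher would have to translate.* The mode of administration is not stated, and an assistant unaware of allocation supports the assessments. Someone who speaks Chinese but reads only English could be interviewed with the Chinese form. At baseline, allocation has not yet occurred, so the assessor cannot be influenced by arm.
- *That the other questionnaires share the fault.* The sections on COM-B and on quality of life fix no language, so there is nothing there to contradict.

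**Conclusion.** The inconsistency is real and limited in reach. Any participant who both speaks and reads only English could not complete PASE as specified. For someone who speaks Chinese but reads only English, the difficulty depends on a mode of administration that the article leaves open. The number affected is unknown; the range of 0.3 to 6 expected among 30 rests entirely on assumed shares, and zero is plausible. The damage falls on the validity and completeness of one primary measure, and on what the trial can conclude about that measure's suitability. The overall data-completeness decision is unlikely to turn on it. No inferential result is at risk, since none is planned.

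**What to change.** Reconcile the two sections in one of two ways.

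1. Amend Subjective measures of PA along these lines: *Each participant completes PASE in the preferred reading language, using the Chinese version or an English version. The version chosen at T1 is used again at T2 and T3 and is recorded on the case report form.*
2. Or restrict the language criteria under Eligibility criteria for participants to people who can complete the Chinese form.

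The first costs a sentence and one field on the case report form. Its drawback is that group summaries would pool two language versions; holding the version constant within a person keeps each individual's change on a single form. The second keeps a single instrument but narrows the population.

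The Trial status section says recruitment was in progress at submission, so the version already given to any English-only reader should be documented.
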